## Abstract

**Background:** Most preterm infants fail to aerate their immature lungs at birth and need respiratory support for cardiopulmonary stabilization. Cord clamping before lung aeration compromises cardiovascular function. Delaying cord clamping until the lung has aerated may be beneficial for preterm infants by optimizing hemodynamic transition and placental transfusion. A new purpose-built resuscitation table (the Concord) has been designed making it possible to keep the cord intact after preterm birth until the lung is aerated and the infant is respiratory stable and breathing [Physiological-Based Cord Clamping (PBCC)]. The aim of this study is to test the hypothesis whether stabilizing preterm infants by PBCC is at least as effective as the standard approach using time-based Delayed Cord Clamping (DCC).

**Study design:** This is a randomized controlled non-inferiority study including 64 preterm infants born at <32 weeks of gestation. Infants will be randomized to either the PBCC approach or standard DCC. In case of PBCC, infants will be stabilized with an intact umbilical cord and the cord will only be clamped when the infant is considered respiratory stable, defined as the establishment of regular spontaneous breathing, a heart rate ≥100 bpm and oxygen saturation above 90% while using inspired fraction of oxygen (FiO2) < 0.40. The Concord will be used, which allows giving respiratory support with an intact umbilical cord. In the DCC group infants are clamped first before they are transferred to the standard resuscitation table for further treatment and stabilization. Cord clamping is time-based and delayed at 30–60 s. The primary outcome will be the time to respiratory stability of the infant, starting from birth. Secondary outcomes will include details of stabilization, important clinical outcomes of prematurity and maternal safety outcomes.

**Discussion:** We expect that PBCC using the Concord may reduce major morbidities and mortality in preterm infants. The current study protocol will assess the effectivity of stabilization. Once effectivity of stabilization is confirmed, we will start a large multicenter randomized clinical trial to investigate whether PBCC reduces mortality and morbidity in preterm infants compared to the standard approach.

**Trial registration:** Netherlands Trial Registry NTR7194, registered on April 20th, 2018.

## Introduction

Preterm infants are most vulnerable immediately after birth. Management in the first minutes of life can have a major impact on important short and long-term morbidities associated with prematurity (1, 2). During the transition to extra-uterine life, lung aeration at birth is pivotal for the major physiological changes in respiratory and cardiovascular function that are required for survival after birth (3, 4). Most preterm infants fail to aerate their immature lungs and require respiratory support at birth (5). This is commonly conducted after umbilical cord clamping, which in experimental studies has shown to compromise cardiovascular function (6).

Preterm infants could benefit from a placental transfusion (blood from the placenta to the infant) when cord clamping is delayed. A recent meta-analysis comparing delayed cord clamping (DCC) with immediate cord clamping (ICC) in preterm infants indeed showed an increased hematocrit, less blood transfusions, a decrease in neonatal mortality, and a trend toward less intraventricular hemorrhages (IVH) (7). However, in most studies DCC was performed using a fixed time-point of 30–60 s while placental transfusion is only complete after 3 min (8). In addition, preterm infants needing immediate interventions for stabilization or resuscitation were clamped immediately and thus excluded, while these infants have the highest risk of complications.

While the rationale of most cord clamping studies was based on increased placental transfusion, we recently demonstrated in preterm lambs that delaying cord clamping until ventilation onset prevents a significant reduction in cardiac output (6). This also prevented large fluctuations in systemic and cerebral blood pressures and flows, and concomitant bradycardia and hypoxia after ICC (9). This finding may explain the bradycardia and hypoxia that is often observed in preterm infants after ICC (10–12). Avoiding these adverse effects may decrease the risk of mortality and (cerebral) morbidity (13). The adverse effects could possibly be avoided when preterm infants are first stabilized with the cord intact and only clamped when the infant is respiratory stable. We called this physiological-based cord clamping (PBCC) as the moment of cord clamping is based on the clinical condition of the infant (14).

Some studies in preterm infants have been performed where respiratory support was provided before the cord was clamped. These protocols all used a time-based approach, with cord clamping at 60 s, 90 s, and 2 min after birth, respectively (15–17). PBCC is based on the clinical condition of the infant, but no clear criteria are available to define when an infant is respiratory stable. We will use the definition that the infant has established regular spontaneous breathing with oxygen saturation (SpO2) above 90%, heart rate > 100, and oxygen need < 40%. This is based on previous observations of stabilization of preterm infants showing that most infants were breathing with CPAP within 5 min after birth (18). When performing PBCC the primary aim is lung aeration and sufficient increase in pulmonary blood flow before the cord is clamped and by using our definition we expect to be able to achieve these aims.

Leiden University Medical Center (LUMC) developed a new purpose-built resuscitation table, the Concord (Figure 1). This mobile resuscitation table is designed to provide full standard care in stabilization of preterm infants at birth while the cord remains intact. All equipment that is needed for stabilization and resuscitation is incorporated in the table (www.concordneonatal.com). We recently completed a feasibility study in preterm infants demonstrating that PBCC using the Concord was feasible and safe (19). We observed less bradycardia and hypoxia at birth, supporting the more stable hemodynamic transition observed in animal studies. In addition, the average cord clamping time was more than 4 min, which may allow preterm infants to benefit from a more optimal placental transfusion. This protocol is designed to assess the effectivity of the procedure and to test whether stabilization of preterm infants according to PBCC using the Concord is at least as effective as stabilization according to the standard approach using the standard table.

**Figure 1 F1:**
[figure not shown]
The Concord, a mobile resuscitation table specially designed to provide full standard care in stabilization of preterm infants at birth while the cord remains intact.

### Aim of the Study

To investigate whether stabilization of preterm infants according to PBCC using the Concord is at least as effective as stabilization according to the current routine approach using a standard resuscitation table.

## Study Design and Population

### Study Design

Randomized controlled non-inferiority study in three centers (Leiden University Medical Center, Erasmus MC University Medical Center and Amsterdam University Medical Centers). The study will be performed in the delivery room or operating room in case of a cesarean section. Infants will be randomized to either stabilization according to PBCC using the Concord (Figure 2), or according to the standard approach using the standard resuscitation table (Figure 3). The study is approved by the LUMC Institutional Review Board (IRB, P18.025) and is registered in the Netherlands Trial Register (NTR7194).

**Figure 2 F2:**
[figure not shown]
Illustration of the Physiological Based Cord Clamping approach using the Concord. Stabilization of the infant is performed while the cord is intact and the cord will be clamped after the infant is respiratory stable.

**Figure 3 F3:**
[figure not shown]
Illustration of the routine Delayed Cord Clamping approach using the standard resuscitation table. Stabilization of the infant is performed after delayed cord clamping (30–60 s).

### Study Population

Infants born prior to 32 weeks of gestational age in one of the three centers may be included in the study. Vaginally and cesarean delivered infants may be included.

Exclusion criteria are significant congenital malformations influencing cardiopulmonary transition, signs of placental abruption or placenta praevia and signs of severe fetal distress necessitating an emergency cesarean section.

Baseline characteristics will be recorded, including gestational age, birth weight, sex, and single or twin deliveries.

### Primary Outcome

The primary outcome will be the time needed to stabilize the infant, starting from birth. Stable is defined as the establishment of regular spontaneous breathing, a heart rate ≥ 100 bpm and oxygen saturation above 90% while using FiO2 < 0.40.

### Secondary Outcomes

Multiple secondary outcomes will be collected, concerning transition of the infant as well as short-term neonatal and maternal outcomes and the procedure itself.

#### Outcomes Relating to the Transition of the Infant

The time point after birth when respiratory support was started and oximeter signals could be interpretedThe occurrence the PBCC approach could not be performed and reason whyFailure of reaching respiratory stability within 10 min from birthDuration of mask ventilation givenAverage pressures given during mask ventilationAverage pressure given during mask Continuous Positive Airway Pressure (CPAP)Oxygen saturation and heart rate in the first 10 min from birthTime point of cord clampingProblems occurring with the cord before cord clampingOccurrence of the need for cord clamping before stabilizationThe need for intubation in the delivery roomThe rate of hypothermia at admission in the NICUApgar scores at 1, 5, and 10 minEchocardiography measurement: ductal flow ratio at 1 h of age

#### Short-Term Maternal Outcomes

Perinatal blood lossThe rate of postpartum hemorrhageThe rate of surgical site wound infection after cesarean section

#### Short-Term Neonatal Outcomes

Mortality at 28 days postnatal age and at NICU dischargeHemoglobin and hematocrit levels within 24 hNeed for intubation and mechanical ventilation in the NICUSurfactant treatmentFrequency and duration of phototherapyNumber of erythrocyte transfusionsNecrotizing enterocolitisIntraventricular hemorrhageBronchopulmonary dysplasiaRetinopathy of prematurity

The parents and the health care providers will be asked to fill in a short questionnaire concerning the birth and stabilization. The questionnaire will also contain questions whether they were satisfied and felt comfortable with the approach.

### Sample Size Calculation

There is no data available concerning the effectiveness of stabilization during PBCC and comparing PBCC with standard approaches. Few studies have performed initial respiratory support before cord clamping, but all of them used predefined timing of cord clamping, varying from 30 to 120 s. Data from our feasibility study showed a median time to obtain respiratory stability of 4:23 min [IQR 3:00–5:11] when PBCC is performed.

Using the routine approach the mean time needed to stabilize an infant, starting from birth, is 5 ± 2 min (unpublished data, Leiden database). If there is truly no difference for the time needed to stabilize an infant between the standard approach and PBCC, then 64 infants (32 in each treatment arm) are required to have 80% power to assess whether the lower limit of a one-sided 97.5% confidence interval (or equivalently a 95% two-sided confidence interval) around the difference in the mean-time to stabilization (mean time in the standard group minus mean time in the experimental treatment group) will be above the non-inferiority limit of −75 s. We have chosen the non-inferiority level of 75 s, because this difference is still acceptable according to the current clinical guidelines. We will take in consideration that 7% of infants (unpublished data, Leiden database) will not reach our primary endpoint set for stabilization, because they need continuous PPV, with or without intubation. These infants will be included in all intended analyses.

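### On the protocol's own inputs, 64 infants give about 70% power, not 80%, for the stated one-sided 97.5% confidence interval

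*Protocol article*

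**What the plan says.** Everything needed for the calculation is in one section of the protocol article, Sample Size Calculation.

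- **Variability:** "the mean time needed to stabilize an infant, starting from birth, is 5 ± 2 min" under routine care, taken from an unpublished local database.
- **True difference:** zero. The sentence opens with "If there is truly no difference for the time needed to stabilize an infant between the standard approach and PBCC".
- **Decision rule:** the lower limit of the interval for standard minus experimental "will be above the non-inferiority limit of −75 s".
- **Confidence level:** given in two forms, "one-sided 97.5% confidence interval (or equivalently a 95% two-sided confidence interval").
- **Result:** "64 infants (32 in each treatment arm) are required to have 80% power to assess whether the lower limit of a one-sided 97.5"% interval clears that limit.

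The section also expects 7% of infants not to reach the endpoint. It keeps them in every analysis and states no inflation of the sample size for them. The Statistical Analysis section does not restate a confidence level for the non-inferiority comparison.

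**The concern.** The sentence is complete: it gives the standard deviation, margin, true difference, confidence level, power and sample size. A reader can therefore check it, and the sample size does not follow from the rest.

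This is the calculation for the primary outcome. The Discussion makes the result the condition for starting a large multicenter trial, so the chance of missing non-inferiority when the approaches are equal bears directly on that decision. If power is overstated, an inconclusive result is more likely than readers are told.

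The mismatch also matters for the error rate. The sample size fits one confidence level and the text names another. If the two were later reconciled by moving to a 90% two-sided interval, the false non-inferiority rate would double from 2.5% to 5%. Nothing in the document suggests that this is intended, and the Sample Size Calculation already names the 95% two-sided interval. The consequence that is certain is the wrong power.

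**Working it through.** **Inputs**, all from the Sample Size Calculation: SD σ = 2 min = 120 s, taken as common to both arms; margin M = 75 s; true difference 0; n = 32 per arm; one-sided α = 0.025; power 80%.

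**Formula** (normal approximation, true difference 0): n per arm = 2 (z₁₋α + z₀.₈₀)² σ² / M².

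**1. Reproducing the printed 64.** With one-sided α = 0.05:

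2 × (1.645 + 0.842)² × 120² / 75² = 31.7, rounded up to 32 per arm, or 64 in total.

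This is the printed figure. Power at 32 per arm is then 80.4%. With the t distribution it is 79.6%, and 33 per arm (66 in total) would be needed.

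**2. The level that the text states.** With one-sided α = 0.025:

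2 × (1.960 + 0.842)² × 120² / 75² = 40.2, rounded up to 41 per arm, or 82 in total. The noncentral t calculation gives 42 per arm, or 84 in total.

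The shortfall is 82 − 64 = 18 to 84 − 64 = 20 infants, which is 28% to 31% of 64.

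**3. Power at 32 per arm and one-sided 0.025.**

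- Standard error = 120 × √(2/32) = 30 s.
- Margin over standard error = 75 / 30 = 2.5.
- Power = Φ(2.5 − 1.96) = Φ(0.54) = 70.5%. The noncentral t gives 69.2%.

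| One-sided α | n per arm for 80%, normal (t) | Power at 32 per arm, normal (t) |
|---|---|---|
| 0.025 (stated) | 41 (42) | 70.5% (69.2%) |
| 0.05 | 32 (33) | 80.4% (79.6%) |

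**4. What would rescue 80% at 32 per arm and one-sided 0.025** (normal approximation). Changing one input at a time:

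- a margin of 30 × (1.960 + 0.842) = about 84 s; or
- a true advantage for PBCC of 84 − 75 = about 9 s; or
- an SD of 75 / [√(2/32) × (1.960 + 0.842)] = about 107 s.

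The section states none of these.

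**5. Other routes to 64.**

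- *Smaller SD in the PBCC arm.* The feasibility IQR of 3:00 to 5:11 spans 131 s. Assuming normality, the SD is 131 / 1.349 = about 97 s. Averaging the variances gives √[(120² + 97²)/2] = about 109 s. That needs 34 per arm (68 in total), and power at 32 per arm is 78.5% (77.2% with t). It comes close but does not give 64 at 80%, and the text does not say this SD was used.
- *Inflation for the 7%.* This moves the total further away: 82 / 0.93 = 88.2, so 89; at one-sided 0.05, 64 / 0.93 = 68.8, so 69.
- *Planning for the Mann-Whitney test.* Allowing for its efficiency relative to the t-test under normality also raises the required number.

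**The case against.** The strongest counter-argument is rounding. The SD is printed in whole minutes and comes from a database that the reader cannot see. Any value from 1.5 to 2.5 min (90 to 150 s) would print as 2, and across that range power at 32 per arm and one-sided 2.5% runs from about 92% to about 52%. An unrounded SD of 1.78 min (107 s) would give 80%. It is therefore possible that the unrounded data support the claim. This part stands: the 70% holds for an SD of 120 s, and the true SD may differ. It does not rescue the sentence. The printed SD is the only one given, and with it the one-sided 5% formula lands on 32 per arm, which makes a slip in the level the likelier cause.

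That cause remains an inference, and the match to 64 holds under the normal approximation only. The mismatch between stated inputs and stated power does not depend on the cause.

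The 70% also takes the infants as independent, with a complete and roughly normal time for each. The protocol expects 7% not to reach the endpoint and allows twins to be allocated to the same arm. The figure should be given as conditional on the stated inputs. The same conditions apply to the printed 80%.

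Finally, an article condenses a fuller protocol. That can explain omitted detail, but here the inputs are present and disagree with the result.

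**Conclusion.** The concern holds. For an SD of 120 s, a margin of 75 s, no true difference, 32 independent infants per arm and a one-sided 97.5% interval, power is about 70% (70.5% normal, 69.2% t), roughly 10 percentage points below the stated 80%. If the approaches are equal, the chance of failing to show non-inferiority is about 30% (29.5% to 30.8%), not 20%. At the stated level, 80% power needs 82 to 84 infants. That one-sided 5% was used in place of 2.5% is the most plausible explanation but cannot be confirmed from the document. The decision rule itself is not in error; the stated power is, and it must be corrected.

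**What to change.** Keep the one-sided 97.5% (two-sided 95%) interval as the decision rule and replace the power statement in the Sample Size Calculation with wording such as:

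*With 64 infants (32 per arm), an SD of 120 s, a margin of 75 s, no true difference and a one-sided 2.5% level, power is about 70%. Power of 80% under the same assumptions would need 82 to 84 infants.*

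Repeat in the Statistical Analysis section that non-inferiority is judged on the two-sided 95% interval, so that the level is fixed in both places. If the database SD before rounding was smaller and was the one used, print it and show that it yields 64.

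The cost is one corrected sentence and a less favorable stated power. No extra infants are needed to make the statement true, but the shortfall in power remains. A sponsor who wants 80% at the stated level has to recruit 18 to 20 more infants on these inputs. Adopting a one-sided 95% interval would make 64 consistent under the normal approximation, but it doubles the false non-inferiority rate to 5% and would have to be stated and justified openly, before any outcome data are seen.

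### Infants who never reach stability are kept in a comparison of mean times without being given a time, so the primary contrast is not defined as written for an expected 4 to 5 of 64 infants

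*Protocol article*

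**What the plan says.** The Primary Outcome section defines a time: "The primary outcome will be the time needed to stabilize the infant, starting from birth". The Sample Size Calculation section sets the contrast as "mean time in the standard group minus mean time in the experimental treatment group" and requires the lower confidence limit to lie above −75 s. The planning value is that "the mean time needed to stabilize an infant, starting from birth, is 5 ± 2 min (unpublished data, Leiden database").

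The same section expects that 7% of infants "will not reach our primary endpoint set for stabilization, because they need continuous PPV", with or without intubation. It then commits: "These infants will be included in all intended analyses".

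Ten minutes appears twice elsewhere. Under Outcomes Relating to the Transition of the Infant, not being stable by 10 min is a secondary outcome. In the summary of the PBCC operating procedure, 10 min is the upper limit for clamping. Neither is linked to the scoring of the primary outcome. The Statistical Analysis section offers a t-test or a Mann-Whitney test for continuous data and a logistic regression for the primary outcome. It does not say how infants without a time enter any of them.

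**The concern.** An infant who never becomes stable has no time to stability. Such an infant can enter a mean only with an assigned value, or enter a restricted mean under a stated horizon. The protocol promises inclusion but supplies neither, and it does so in the section that fixes the effect measure and the margin.

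The choice matters for the conclusion. Leaving these infants out contradicts the text and removes the worst outcomes, so an arm with more failures looks faster. If PBCC were that arm, the omission would favour non-inferiority. Assigning a long time keeps them but widens the SD and lowers power. The trial is unblinded, so a rule chosen once outcomes are known would be open to challenge.

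**Working it through.** **Inputs from the Sample Size Calculation section.** Mean 300 s and SD 120 s (5 ± 2 min); margin 75 s; 32 per arm; failure share 7%. The true difference is zero ("If there is truly no difference for the time needed to stabilize an infant between the standard approach and PBCC"). The one-sided level is 2.5% ("the lower limit of a one-sided 97.5% confidence interval (or equivalently a 95% two-sided confidence interval"). The claim is "64 infants (32 in each treatment arm) are required to have 80% power".

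**Step 1: the plan's own figure.** n per arm = 2(z₁₋α + z₀.₈₀)² × SD² / margin².
- One-sided 2.5%: 2 × (1.960 + 0.842)² × 120² / 75² = 40.2, so 41 per arm (82 in total).
- One-sided 5%: 2 × (1.645 + 0.842)² × 120² / 75² = 31.7, so 32 per arm (64 in total).

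The stated 64 is not reproduced at the stated level. It matches one-sided 5% with SD 120 s and no allowance for the 7%. At one-sided 2.5% and 32 per arm, SE = 120 × √(2/32) = 30 s and 75/30 = 2.5. Power is Φ(2.5 − 1.96) = 71%, or 69% with the t distribution: about 70%. This shortfall is a separate error and does not come from the 7%.

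**Step 2: how many infants.** 0.07 × 64 = 4.5 expected. The chance of at least one is 1 − 0.93⁶⁴ = 99%.

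**Step 3: leverage on the difference.** The protocol gives no time for these infants, so 600 s is an assumption taken from its 10-min failure outcome.
- One infant scored at 600 s rather than 300 s moves an arm mean by 300/32 = 9.4 s.
- With four failures under PBCC and one under standard care, and a mean of 300 s among stabilised infants in both arms, PBCC = (28 × 300 + 4 × 600)/32 = 337.5 s and standard = (31 × 300 + 600)/32 = 309.4 s. The difference is −28.1 s, and 28.1/75 = 38% of the margin.
- If the five infants are dropped, the difference is 0 s.
- With independent 7% risks in both arms, a gap of three or more failures in either direction has a probability of about 21%.

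**Step 4: effect on SD and power.** There are two readings of 5 ± 2 min.
- *It already includes these infants.* The SD stays at 120 s and power is about 70%, as in step 1.
- *It describes only the 93% who stabilise* (assumption), with 7% in each arm scored at 600 s. Variance = 0.93 × 120² + 0.93 × 0.07 × (600 − 300)² = 13,392 + 5,859 = 19,251, so SD = 139 s. SE = 139 × √(2/32) = 34.7 s and 75/34.7 = 2.16. Power is Φ(2.16 − 1.96) = 58%, or 57% with the t distribution. On this reading 80% power needs 2 × (1.960 + 0.842)² × 139² / 75², which gives 54 per arm (108 in total).

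**The case against.** The strongest reply is that this is a condensed article. The principle, inclusion of every infant, is fixed, and the scoring rule is the kind of detail an analysis plan sets. A natural 10-min horizon already exists. That stands in part: an unseen document may hold the rule, and the text does not show that none exists. But the article itself joins a mean difference to a promise to include infants with no time, and the two do not fit together without a rule. The Mann-Whitney option does not close the gap. Ranking failures worst would give a test, but no mean difference to set against −75 s.

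Three stronger readings are tempting and are not supported:
- A reader might infer that the primary comparison cannot be computed. It can, once a value is assigned; it is only undefined as written.
- A reader might infer that the planning SD leaves these infants out. The wording of the planning value and the unadjusted 64 point that way, but the source of the SD is not described.
- A reader might set 57% against the stated 80% and blame the 7% for the whole gap. The step from 80% to about 70% is the separate sample-size error. At most the step from about 70% to about 57% belongs here.

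It is also fair to say that a 4-versus-1 split is not the typical case. With five failures and equal risk, four or more fall in a named arm with probability 6/32 = 19%, and the resulting shift is still well inside the margin.

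**Conclusion.** The point holds in this form: the primary contrast is not defined as written for an expected 4 to 5 of 64 infants, and at least one such infant is nearly certain. The handling can move the estimated difference by about 9 s per infant, and by about 28 s (38% of the margin) in a 4-versus-1 split. Power at 32 per arm and one-sided 2.5% is about 70% if 5 ± 2 min includes these infants. It is about 57% if it does not and they are scored at 10 min.

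The sizes assume a score of 600 s, a mean near 300 s among stabilised infants, and a 7% failure share in each arm. Infants who stabilise after 10 min would also sit at the cap, so the share there could exceed 7%. No longer cap is considered, because the documents give no basis for one.

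**What to change.** Define the primary variable as time from birth to stability restricted to 10 min, with every infant not stable by then scored at 600 s. Compare restricted means (standard minus PBCC) with a 95% confidence interval against −75 s. Report the proportion not stable at 10 min by arm beside it. State whether the planning SD includes non-stabilised infants, and restate SD and power on this scale. If an analysis plan already holds a scoring rule, bring it into the protocol and reconcile it with the mean contrast.

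The rule concerns analysis only, needs no new data, and leaves clinical management untouched. It has three costs:
- The effect becomes a restricted mean, so the protocol should confirm that 75 s is still the intended margin on that scale.
- The cap limits how much a failure counts. If PBCC failed more often, this would soften the difference in its favour, so the failure proportions must be read with the result.
- The stated power becomes less favourable: about 70% or about 57% instead of 80% with 64 infants, or a larger trial (82 or 108 infants) to restore it.
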